### Data management

The project manager has primary responsibility for the maintenance and management of the study database, which will be stored on a password-protected computer in a locked office. Research nurses have responsibility for ensuring the completeness, accuracy and confidential storage of data collected in their respective region from patient questionnaires, during the data collection consultations and from patient charts. Each practice and patient participating in the study has a unique identifying code.

Data will be collected and processed in the following ways:

1. **Questionnaire data**: once received in the practice, the research nurse collects the questionnaires and inputs the data into a master SPSS study database. Questionnaires are stored securely in their regional research centre.

2. **Consultation data**: once complete, the research nurse collects the data collection sheets from the practice and inputs the data into the master SPSS database. Data collection sheets are stored securely in their regional research centre.

3. **Chart search data**: the research nurse enters this data directly from patient notes onto an electronic study database created in Filemaker Pro software. Data can subsequently be exported directly into the master SPSS database using the unique patient identifier as the link field.

In the interests of data accuracy, numerical fields have range limiters to ensure that values outside a particular range cannot be entered; also, random data checks are performed on a regular basis to confirm completeness and accuracy of data. Inter-researcher data entry reliability is ensured by a process of trial data entry by the three research nurses of a sample of 20 questionnaires and consultation data sheets and 10 patient charts data early in the study data collection process. Where discrepancies in data entry are observed between the researchers, discussion will ensue to resolve any ambiguities or disagreement and clarify data collection and entry guidelines. Once all data has been completely entered and checked in the master SPSS database, preliminary analysis can be performed. The data will be sent in this format to the study statistician, who will import the data into Stata software to perform the necessary statistical modelling procedures.

### Data monitoring

Interim results after one year will be presented to an independent data monitoring committee (DMC), made up of a statistician, an epidemiologist, and a clinician with statistical expertise. The role of the DMC will be to:

a) Ensure that no harm is being conducted to study participants

b) Act in an advisory capacity with respect to research governance.

## Qualitative Evaluation

### Introduction

Qualitative research will be conducted after years 1 and 2 of the intervention. It will facilitate evaluation of the intervention based on the experiences of practice staff and patients in delivering and receiving the intervention respectively. It also aims to compare their experiences with those of patients and practitioners in the control practices. The qualitative research will be integrated with the economic and policy evaluations.

### Aims for intervention group (Year 1)

The aims of the qualitative evaluation study with the intervention group at the end of year 1 are to explore:

• How the intervention is implemented

• How the intervention is integrated with other practice activities

• How well practitioners and patients understand the intervention

• Whether elements of the intervention are particularly important or problematic

• Attitudes to the cost of implementing the intervention for practices and patients.

### Aims for control group (Year 1)

The aims of the qualitative evaluation study with the control group at the end of year 1 are to explore:

• The nature of secondary prevention care implemented during the study period

• The impact of any policy changes during that time.

### Aims for intervention group (Year 2)

The aims of the qualitative evaluation study with the intervention group at the end of year 2 are to explore:

• Changes in how the intervention is implemented and the reasons why

• Whether the aims of the intervention have been achieved

• The feasibility of the intervention being continued after the study ends

• Whether patients would be willing to pay for such a service.

### Aims for control group (Year 2)

The aims of the qualitative evaluation study with the control group at the end of year 2 are to explore:

• Changes in how secondary prevention care is implemented and the reasons why

• The impact of any policy changes during that time.

### Data collection and analysis

The qualitative research will be guided by the principles of the methodology of grounded theory. Practitioners and patients will be purposively sampled using theoretical and maximum variation sampling methods to ensure a variety of characteristics and experiences. Small and large practices that reflect a mixture of rural, urban, deprived and affluent locations will be selected.

The data will be collected using focus groups and individual semi-structured interviews. The focus groups aim to explore the diverse experiences of patients receiving the intervention. They will include men and women who vary in the nature of their heart disease, length of time since diagnosis, age and ethnic group (if possible). Participants will be invited to participate by letter which will explain the purpose of the interviews, followed by a telephone call from the practice nurse. Their reasons for not wishing to participate in the interviews will be recorded. The research nurses will act as observers of the focus group and will take notes of the discussion and map the interaction of the participants. Individual interviews with some patients will be used to clarify and to explore in more detail issues discussed in the focus groups. Free text comments in the patient questionnaire that forms part of the economic evaluation will also form part of the qualitative evaluation.

Individual interviews will also be conducted with GPs and practice nurses who are involved in implementing the intervention, with more interviews being conducted with the nurses, who tend to be responsible for the clinics. The interviews and focus groups will be audio-taped with the participants' consent and transcribed verbatim.

The interviews and focus groups will be divided between two qualitative researchers. The development of an interview schedule and role plays of the interviews by the researchers will be used to standardise the interviews and minimise the effects of the researchers on the data.

Data on the actual process of care will also be collected using overt observation methods by the research nurses. This will strengthen the validity of the interview data by comparing what practitioners actually do with what they say they do and will act as a quality control measure. Field notes of the research nurses' observations of the intervention based on their regular contacts with the practices will also form part of the qualitative data. These will be explored in more detail in a focus group with the research nurses.

The control practices will act as negative cases and will test whether the data from the intervention practices are unique to them or are shared with non-intervention practices. This will strengthen the reliability of the data from the intervention practices. The characteristics of the participants will be matched to the characteristics of participants in the intervention practices.

The data collection and analysis will be iterative and will continue until data saturation is achieved. Analysis will be conducted using the constant comparative method and will be facilitated by importing the interview transcripts into the computer software programme Nudist. A summary of the main findings will be sent to a sub-sample of patients and practitioners from the intervention and control groups in each of the 3 centres who were interviewed to validate our findings.

The number of interviews will be divided equally among the 3 centres. The number of interviews to be conducted among patients and practitioners is shown in Tables 1 and 2.

**Table 1 T1:** Qualitative Research with Intervention Groups

	**Focus Groups**			**Individual Interviews**			
	
	Patient Focus Groups	Research Nurse Focus Groups	Total Focus Groups	Patient Interviews	Practice Nurse Interviews	GP Interviews	Total Interviews
Year 1	3	1	4	6	6	3	15
Year 2	3	1	4	6	6	3	15
Total	6	2	8	12	12	6	30

**Table 2 T2:** Qualitative Research with Control Groups

	**Focus Groups**		**Individual Interviews**		
	
	Patient Focus Groups	Total Focus Groups	Practice Nurse Interviews	GP Interviews	Total Interviews
Year 1	3	3	3	3	6
Year 2	3	3	3	3	6
Total	6	6	6	6	12

## Economic Evaluation

### Introduction

The economic analysis incorporates both cost minimization analysis and cost effectiveness analysis for the various interventions for the two groups. The basic tasks of the evaluation are to identify, measure, value and compare the costs and outcomes of the alternatives being considered. Costs are likely to fall on patients, their families and the state. The health care resources consumed will reflect the costs of organising and operating the two programmes: intervention and control. These costs will reflect the time input of health professionals and fixed or overhead costs, including any new equipment and capital expenditure. All contacts with the health services are recorded and valued, including general practice contacts, hospital attendances, admissions and drug prescriptions. The patient and family costs include any out-of-pocket expenses and any own time input into the treatment process. Estimates will be made of work and leisure time foregone as part of the treatment alternatives, together with quality of life estimates. Cost-effectiveness analysis is the primary method of economic evaluation with measures of effectiveness taken from the range of primary and secondary outcomes being considered for the two groups.

In the Republic of Ireland, free healthcare is available to patients who qualify under the means-tested General Medical Scheme (GMS), although chronic disease management is not fully supported by this system. Non-GMS patients are required to pay for all of their own healthcare costs. In order that the findings of the SPHERE study will be translatable into practice within the existing healthcare systems, non-GMS patients in the Republic of Ireland will be required to pay for SPHERE-related visits to their general practice as normal. The cost of extra visits by GMS patients will be borne by the practices. The research team acknowledges that this may have an impact on recruitment of both practices and patients, although in a similar study the impact on patient recruitment was not substantial [28].

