### Randomised controlled trial analysis

Primary outcomes include:

• Blood pressure

• Total cholesterol

• Physical and mental status as measured by the SF-12

• Hospital re-admissions.

Secondary outcomes include:

• Measure of the process of care

SPHERE visits

Total number of GP visits

Total number of hospital OPD visits

Recording of risk factors in GP records

• Body Mass Index/Waist-Hip Ratio

• Exercise: Godin Leisure-Time Exercise Questionnaire

• Smoking status

• Diet: DINE, including question regarding portions of fresh fruit and vegetables

• Adherence to medication (Medication Adherence Report Scale MARS-5).

All results are analysed using SPSS and Stata statistical software. Statistical modelling is carried out using Stata statistical software which has a facility for complex survey sample analysis that allows for adjustments in data analysis based on design effects, planned or unplanned. Statistical significance will be taken at the 5% level for both primary and secondary outcomes. The analysis examines intervention vs control groups on study completion, as opposed to looking at changes in the intervention and control groups from baseline.

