### Aim

The aim of the economic analysis is to provide both cost minimization analysis and cost-effectiveness analysis of secondary prevention of heart disease in general practice. The cost effectiveness analysis provides information on the marginal costs and effects of the intervention relative to the alternative through the calculation of an incremental cost-effectiveness ratio. In situations where there is no significant difference in effects, the use of cost minimization analysis allows the reporting of cost differences only.

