### Outcome measures

Both primary and secondary outcome measures are collected as part of the randomised controlled trial analysis. The cost-effectiveness analysis will be based primarily on intermediate endpoints. However, some intermediate endpoints, such as blood pressure, are uni-dimensional measures and may or may not have a high correlation with a final endpoint, such as life years gained. Hence the need to explore the estimation of final endpoints in the analysis, where possible, thereby allowing much greater scope to make comparisons of cost-effectiveness with other studies.

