### Analysis

The analysis will use standard economic analysis for the calculation of costs and incremental cost-effectiveness ratios. Unit costs will be applied to the resource use data to calculate the various costs of care. Comparisons between the intervention and control groups will be made on the various primary and secondary outcomes and costs will be assigned accordingly. The analysis will allow us to consider whether significant differences emerge between intervention and control groups in terms of the various outcome measures. We will examine whether the intervention is associated with overall cost increases or cost decreases and link the cost changes to incremental gains in effectiveness, where they exist.

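### The economic analysis names no lead effectiveness measure and links costs to effects only where gains appear, so it permits ratios to be limited to outcomes that came out well

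*Protocol article*

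**What the plan says.** Four subsections of Economic Evaluation in the protocol article bear on the point.

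- **Introduction.** Cost-effectiveness analysis is the primary method, with "measures of effectiveness taken from the range of primary and secondary outcomes being considered for the two groups".
- **Aim.** The result is to be an incremental cost-effectiveness ratio. A second route is added: "In situations where there is no significant difference in effects, the use of cost minimization analysis allows the reporting of cost differences only".
- **Outcome measures.** "The cost-effectiveness analysis will be based primarily on intermediate endpoints". Blood pressure is mentioned as an example of such an endpoint, with a warning that it may not track a final endpoint such as life years. The text continues: "Hence the need to explore the estimation of final endpoints in the analysis, where possible".
- **Analysis.** "Comparisons between the intervention and control groups will be made on the various primary and secondary outcomes and costs will be assigned accordingly". Further down, this subsection undertakes to "link the cost changes to incremental gains in effectiveness, where they exist".

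The outcome list is under Randomised controlled trial analysis: four primary entries and six secondary ones. That section adds: "Statistical significance will be taken at the 5% level for both primary and secondary outcomes".

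Nowhere is one outcome named as the denominator of the main ratio. Nor does the article say that ratios will be given for every outcome whatever the result.

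**The concern.** A condensed article may leave the choice of effectiveness measure to a fuller plan, and that alone would not be worth raising. The difficulty is that this article states a rule, and the rule depends on the results. The candidates are the trial's outcome list, the link from cost to effect is made where gains appear, and where effects are not significant the effect side may be dropped.

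An incremental ratio divides a cost difference by an effect difference. If a ratio is shown only for outcomes whose observed effect was favourable, the denominators shown have been selected for being large. On average they overstate the true effect, and cost per unit of effect is then understated. The economic results also feed into the Policy Evaluation, which compares secondary prevention policy in two health systems. The article itself warns that an intermediate endpoint may correlate poorly with a final one, so the choice of outcome can matter to the reader's conclusion.

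**Working it through.** The article states no ratio, threshold or economic power, so there is no figure to reproduce. The check has two parts: what the text fixes, and how large the selection effect could be.

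**1. What the text fixes**

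| Question | Where answered | Answer |
|---|---|---|
| Which outcome is the main denominator? | Introduction; Outcome measures | The range of trial outcomes, mainly intermediate endpoints; none named |
| When is cost linked to effect? | Analysis | Where a gain exists |
| What if the effect is not significant? | Aim | Cost differences alone may be reported |
| Are all ratios reported whatever the result? | Nowhere | Not stated |

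**2. Chance of a falsely favourable outcome to link to**

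Inputs:
- Significance level 5% per outcome (Randomised controlled trial analysis). Sidedness is not stated. I assume two-sided, so 2.5% in the programme's favour.
- Number of candidates k. The primary list has four entries. Adding the six secondary entries gives 4 + 6 = 10. Treating all ten as candidates is an assumption.
- No true effect on any outcome, and independent outcomes (assumptions).

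Formula: P(at least one significant favourable result) = 1 − (1 − 0.025)^k.

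- k = 1: 2.5%
- k = 4: 1 − 0.975^4 = 1 − 0.9037 = 9.6%
- k = 10: 1 − 0.975^10 = 1 − 0.7763 = 22.4%

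The entry "Physical and mental status as measured by the SF-12" could count as two scores. With k = 5 the figure is 1 − 0.975^5 = 11.9%.

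Independence is not realistic for these outcomes. Simulating equally correlated null z-scores (200,000 runs) gives:

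| Assumed correlation | k = 4 | k = 10 |
|---|---|---|
| 0 | 9.6% | 22.3% |
| 0.3 | 8.7% | 17.8% |
| 0.5 | 7.8% | 14.4% |

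**3. Size of the distortion when the effect is real but shown only if significant**

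Let μ be the true effect in standard errors, with μ = 1.96 + z(power). Let φ be the standard normal density. The mean estimate, given that it exceeds 1.96, is μ + φ(1.96 − μ)/power. The cost ratio evaluated at that mean effect, with incremental cost unchanged, is μ divided by it.

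| Assumed power | μ | Mean estimate if significant | Overstatement of effect | Cost per unit relative to truth |
|---|---|---|---|---|
| 30% | 1.44 | 2.60 | 1.81 | 0.55 |
| 50% | 1.96 | 2.76 | 1.41 | 0.71 |
| 80% | 2.80 | 3.15 | 1.12 | 0.89 |

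The significance cut-off in parts 2 and 3 belongs to the rule in the Aim subsection. The Analysis subsection speaks only of gains and sets no cut-off.

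**The case against.** The strongest reply is that this is a summary of the economic methods, and that the lead measure would ordinarily be fixed in a fuller plan. That holds for the missing name taken alone. It does not hold for the stated rule that costs are linked to gains where they appear, nor for the switch to cost differences when effects are not significant.

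Second, a reader might infer that the investigators will pick the single best outcome after seeing the data and build the result on it. The documents do not support that. The wording is plural throughout (measures, ratios, various outcomes), which points to several ratios side by side. The analysis also expects to report cost increases as well as decreases. The qualifier about gains may mean no more than that a cost per unit gained cannot be stated where nothing was gained. This stands, and it is why the point is about what the text permits. Several ratios do not cure the problem, however, if only outcomes with gains receive one.

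Third, the Outcome measures subsection narrows the pool to mainly intermediate endpoints, so ten equal candidates is generous. This also stands. The figure for the four primary outcomes is the more cautious illustration, although that list too is not made up only of intermediate endpoints.

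Finally, the percentages are the ordinary multiplicity of the outcome list carried into the economic section. That is fair: they show how much room for selection exists and do not estimate what will happen. The policy work also draws on outcome and qualitative data, so it does not rest on one ratio.

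**Conclusion.** The point holds as a weakness in a stated rule. The economic sections draw effectiveness from a range of outcomes, name no lead measure, and make both the linking of cost to effect and the choice of method depend on the observed result. Selective reporting is permitted, not declared, and a flattering ratio is a tendency that would follow from such selection, not a certainty.

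The illustrative size is about 10% for four candidates and 22% for ten, against 2.5% for one measure named in advance; at correlation 0.5 the first two fall to about 8% and 14%. These figures assume two-sided testing, no true effect and the stated candidate counts. The overstatement factors of 1.12 to 1.81 rest on assumed power of 80% down to 30%. The direction of the bias under selection does not depend on these assumptions. The main trial comparison is unaffected.

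**What to change.** Before the two-year data are seen, amend Economic Evaluation as follows.

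1. In Introduction and Outcome measures, name one effectiveness measure for the main incremental ratio. Which one is the sponsor's choice among outcomes already collected.
2. In Analysis, delete the closing qualifier that restricts the link to cases where gains exist.
3. In Analysis and Aim, state that incremental cost, incremental effect and their ratio will be reported with joint uncertainty whatever the direction or significance of the effect. Where the effect is near zero or negative the ratio cannot be read alone, so the two increments should always stand beside it.
4. Report the results on the other outcomes in full, labelled as secondary, and not only those with gains.

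The cost is a change of wording and a little more analysis, with no new data. The sponsor gives up the freedom to choose the measure after seeing the results.

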### Aim

The aim of the economic analysis is to provide both cost minimization analysis and cost-effectiveness analysis of secondary prevention of heart disease in general practice. The cost effectiveness analysis provides information on the marginal costs and effects of the intervention relative to the alternative through the calculation of an incremental cost-effectiveness ratio. In situations where there is no significant difference in effects, the use of cost minimization analysis allows the reporting of cost differences only.

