**Figure 1 F1:**
[figure not shown]
Flow of Practices and Patients Throughout Trial.

Sample size calculations are based on the following:

• Power of 80% and alpha of 5%.

• Only patients agreeing to participate in the study and completing baseline data collection will be entered into the study. There will, therefore, be 100% uptake at the start of the study. Reasons for non-participation will be documented and recorded, and participation rates will provide a measure of the acceptability of this type of intervention to patients.

• A final completion rate of 70% is anticipated based on similar studies in the West of Ireland 7 (completion rate = 68.7%) and Dublin [28] (completion rate = 93%).

• Practice attrition of 12.5% has been allowed for (though practice attrition in another similar study was only 4% [28]).

• Improvements in the control group as a result of participation in a research study have been anticipated [25].

• Design effects are calculated using intracluster correlation coefficients from data from similar populations in Galway and Scotland ([name], personal communication).

A total sample size of 907 patients recruited from 46 practices gives a varying but minimum power of 80% to detect significant changes in proportions with poor blood pressure and cholesterol control, physical and mental well being (SF-12) and hospital readmissions at two years. (Detailed power calculations are given below). This allows for a final patient follow-up and retention rate of 70% and a practice attrition rate of 10%. The number of practices is rounded up from 46 to 48, to allow equal numbers of practices to be recruited in each of the three study centres. Sixteen practices will therefore be recruited in each of the three centres, eight intervention practices and eight control practices. Twenty patients are recruited in each practice. Final data analysis will incorporate modelling techniques that are more statistically efficient and will ensure greater power to detect significant changes in study outcomes.

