### Cholesterol

36% of Irish patients have a baseline cholesterol level above the upper recommended limit, i.e. greater than 5 mmol/l ([name], personal communication). To demonstrate an improvement of 50% in the intervention group and 20% in the control group requires a sample size of 500 patients. To ensure a final sample of 15 patients per practice, this is inflated by a design effect size of 1.27 (ICC = 0.019; [name], personal communication) to give a sample of 635 patients from 42 practices. This is increased to 907 patients from 46 practices to allow for final follow up and response rate of 70% and practice attrition of 10%.

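### The economic plan permits cost-only reporting when effects are not significantly different, which takes a non-significant superiority test as evidence of equal effect

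*Protocol article*

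**What the plan says.** The Aim section of the Economic Evaluation in the protocol article announces both a cost-minimisation and a cost-effectiveness analysis. It gives one condition under which costs may be reported alone: "In situations where there is no significant difference in effects, the use of cost minimization analysis allows the reporting of cost differences only".

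Three other places bear on how this is read:

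- The Introduction to the Economic Evaluation ranks the methods: "Cost-effectiveness analysis is the primary method of economic evaluation". Its effect measures are drawn from the trial's primary and secondary outcomes. It contains no significance condition.
- The Analysis section of the Economic Evaluation promises to compare the groups on these outcomes and to "link the cost changes to incremental gains in effectiveness, where they exist".
- The Randomised controlled trial analysis section sets the test level: "Statistical significance will be taken at the 5% level for both primary and secondary outcomes".

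The Sample Size Calculation section bases the trial size on at least 80% power to detect differences. No section gives an equivalence or non-inferiority margin, or a confidence-interval criterion for calling two effects equal.

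**The concern.** Cost minimisation compares costs alone on the footing that effects are the same. That footing needs evidence of sameness, normally a confidence interval lying inside a margin set in advance. The sentence in the Aim accepts the absence of a significant difference instead. In a superiority trial without a margin, that absence may reflect imprecision as easily as equality.

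Two things are at stake. First, the intervention adds staff training, four-monthly consultations for two years and nurse support. A real benefit that misses significance could appear in the economic result only as extra cost, and a non-significant harm could appear only as a saving. The Policy Evaluation section intends to use the results of the economic appraisal, so the omission could carry forward.

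Second, the condition does not say which effect must be non-significant. With several primary and secondary outcomes available, the same cost data could lead to an incremental ratio for one outcome and to costs only for another, with the choice depending on the results.

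**Working it through.** The check asks how often a non-significant result would arise when the effect is real, and how wide the interval around a null result would be.

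**Inputs from the protocol** (Sample Size Calculation; Power Calculations – Further Detail)

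- Final sample: 635 patients from at least 42 practices, about 15 per practice.
- Planned relative improvement: 50% in the intervention group, 20% in the control group.
- Cholesterol: 36% above the limit at baseline, so 0.80 × 36 = 28.8% in control and 0.50 × 36 = 18% in intervention; ICC 0.019.
- Systolic blood pressure: 44% at baseline, so 35.2% and 22%; ICC 0.011.
- Admissions: 43%, so 34.4% and 21.5%; ICC 0.006.
- Alpha 5%. I assume two-sided tests, because sidedness is not stated, and a 1:1 split.

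**Reproducing the plan's own figures.** The usual two-proportion formula with continuity correction, 80% power and rates rounded to whole percentages gives:

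- cholesterol, 29% vs 18%: 250 per arm, 500 in total, as stated;
- blood pressure, 35% vs 22%: 204 per arm, 408 in total, as stated.

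Then 500 × 1.27 = 635 and 635 / 0.70 = 907, also as stated. The admissions figure of 356 is not reproduced by this method. It is not used below; only the admissions rates and ICC are.

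**Effective sample size.** Variance inflation = 1 + (15 − 1) × ICC, and effective n per arm = 635 / inflation / 2.

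- Cholesterol: 1 + 14 × 0.019 = 1.266; n = 250.8
- Blood pressure: 1 + 14 × 0.011 = 1.154; n = 275.1
- Admissions: 1 + 14 × 0.006 = 1.084; n = 292.9

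**Chance of non-significance when the effect is real.** With d = p1 − p2 and m the mean of p1 and p2,

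power = Φ{ [ d√n − 1.96 √(2m(1 − m)) ] / √( p1(1 − p1) + p2(1 − p2) ) }.

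For cholesterol at the full planned effect: d√n = 0.108 × √250.8 = 1.710; m = 0.234, so √(2m(1 − m)) = 0.5987 and 1.96 × 0.5987 = 1.1735; the denominator is 0.5938. Power = Φ(0.537 / 0.5938) = Φ(0.904) = 0.817, so non-significance has probability 0.183.

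The same formula gives these probabilities of a non-significant result:

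| Outcome | Full planned effect (50% vs 20%) | 40% vs 20% (assumed) | 35% vs 20%, half the planned difference (assumed) |
|---|---|---|---|
| Cholesterol | 18% | 54% | 72% |
| Blood pressure | 7% | 39% | 62% |
| Admissions | 6% | 38% | 61% |

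**Width of the interval around a null result.** If both arms showed the planned control rate p, the 95% half-width is 1.96 √(2p(1 − p)/n).

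- Cholesterol: 1.96 √(2 × 0.288 × 0.712 / 250.8) = 7.9 points, against a planned difference of 10.8 (73%).
- Blood pressure: 1.96 √(2 × 0.352 × 0.648 / 275.1) = 8.0 points, against 13.2 (60%).

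Even identical observed rates would therefore leave differences of 60% to 73% of the planned size inside the interval.

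**The case against.** The strongest reply is that the sentence is permissive. It says what cost minimisation allows and does not say that the cost-effectiveness analysis will be abandoned. The Aim promises both analyses, the Introduction makes cost-effectiveness the primary method, and the clinical effects will be reported in the main trial analysis in any case. This stands in part. A reader might infer that the plan switches automatically to costs, or that a non-significant benefit will be set to zero. The wording supports neither. What remains is that non-significance is the only condition given for cost-only reporting, and nothing in the Economic Evaluation limits its use.

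A reader might also take the phrase in the Analysis section, "link the cost changes to incremental gains in effectiveness, where they exist", as a second significance rule. It does not mention significance, so that is inference; it only needs to be read consistently with the repair. Nor can one conclude that joint uncertainty in costs and effects will go unreported. A journal article may leave bootstrap methods, cost-effectiveness planes and acceptability curves to a fuller plan, and silence on them is not a fault.

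On the figures, at the full planned effect the chance of non-significance is modest for blood pressure and admissions, and cholesterol is the weakest of the three. The 40% and 35% reductions are not in the protocol. None of the percentages is the probability that the whole economic analysis reduces to costs, because the governing outcome is not named. All of this is accepted. It limits the size of the point, not the principle.

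**Conclusion.** The point holds as a fault in one stated rule: the protocol permits cost-only reporting on the strength of a non-significant superiority test, with no margin by which equal effect could be judged. The planned sample cannot make that inference safe. Per outcome, the condition would be met about 18% (cholesterol), 7% (blood pressure) and 6% (admissions) of the time with the full planned effects present. With a 40% intervention reduction it would be met about 54% of the time for cholesterol and 39% for blood pressure.

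These figures assume 635 analysed, 15 per practice, equal arms, two-sided 5% tests and the protocol's rates and ICCs; the 40% case is illustrative. The point should be fixed. It is not more serious than that, because the randomised clinical comparison, the sample size and the data collection are unaffected.

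**What to change.** - In the Economic Evaluation, Aim, delete the last sentence. State instead that, for each chosen effect measure, incremental cost and incremental effect will be reported together, with uncertainty adjusted for clustering, whatever the p-value.
- Reserve cost minimisation for an outcome that meets an equivalence margin stated in advance.
- In the Introduction, add a matching description of when cost minimisation applies. Nothing there needs deleting.
- In the Analysis section, make clear that linking costs to effects does not depend on significance.

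The cost is a few sentences and a little extra analysis, with no new data. The change should be made before outcome results are seen, so that the choice of economic method cannot follow them.
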